### Data Analysis

All data will be stored in a secured server for highly sensitive data. Data will be cleaned and analyzed in statistical software packages (ie, SPSS, SAS, and R). Protocol nonadherence will be defined as individuals who fail to complete the baseline and postintervention surveys. Because this pilot study is only being conducted at a single site, a data monitoring committee was not utilized.

Quantitative data on user experience will be analyzed descriptively, to be compared with user data in existing literature. Qualitative user experience data will be reviewed for content and emerging themes through content analysis. Participants’ interview responses will be recorded by research staff. Qualitative responses will be coded and evaluated according to the general domains of (1) ways to improve the design and user interface of the apps; (2) the specific apps that were most helpful (and why); (3) the specific apps that were least helpful (and why); (4) obstacles and barriers to using the apps; and (5) ways to improve the usefulness of coaching calls. Initial coding of the data will be based on a priori domains and will be refined during the analysis process conducted by investigators. Additional themes that are identified will be defined and coded.

Due to the within-subject pre-post design, changes in outcome measures in both cancer patients and caregivers will primarily be analyzed using paired *t* tests. Descriptive statistics will primarily be used to examine whether IntelliCare app use is associated with changes in process variables (ie, mood, social functioning, and health behavior) during the study period. These analyses will be performed separately for patients and caregivers. Because the IntelliCare apps are intended as an intervention package, we will be evaluating the app suite as a whole in breast cancer patients and caregivers rather than selecting specific apps for patients and caregivers. A separate set of analyses will examine associations between changes in cancer patient and caregiver outcomes. Specifically, zero-order correlations will be computed to examine whether improvement in caregiver depression or anxiety symptoms is positively associated with improvement in patient depression or anxiety symptoms. Correlations will also be computed to examine whether improvement in caregiver self-efficacy is positively associated with improvement in patient mood symptoms. The purpose of these analyses is to obtain estimates of effect size that can be used to inform future trials. Additional discussions with cancer clinicians will be used to obtain additional information on possibility effect size and variance estimates [33]. We do not intend to perform any between-group contrast analyses (ie, between patient and caregiver or between different IntelliCare apps).

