### Participants

To limit barriers to entry, inclusion criteria are limited to the following: (1) breast cancer patient or informal caregiver (ie, not receiving compensation for providing care); (2) at least 18 years of age; (3) proficient in English at a sixth grade level; and (4) has a mobile phone or is willing to carry one around if provided. Participants are not required to have a minimum level of familiarity with mobile devices or technology. Participants will be eligible to receive a US $50 gift card for providing user feedback at the end of the study. Study procedures, including the coaching protocol and access to IntelliCare apps, will be identical for both breast cancer patients and caregivers.

A target sample size of 50 (25 patients and 25 caregivers) was chosen, given the exploratory nature of this study. Recruitment of participants will occur in a small breast surgical oncology clinic. Clinics are held on 4 out of 5 weekdays, and the 3 surgical oncologists do not have overlapping clinic times. The recruitment goals were influenced by several factors. First, the patients seen in this clinic are generally early in the breast cancer diagnostic pathway and although it is a time of need for the type of mental health support these apps can provide, it is also a time when it may not be appropriate to recruit them to a study that requires an immediate face-to-face consent and app download process. Second, the logistics of clinic flow, space, and time constraints also influence the pace of recruitment. Overall, 1 to 2 participants per week became the targeted number, which over the course of 29 weeks of active recruitment would yield a sample size between 29 and 58 consented participants.

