The primary objective of this study is to inform the feasibility of a larger randomized trial in a clinical setting [22]. Data on usability and user experience from this sample will enable researchers to make iterative changes for future studies. A secondary objective of this study is to provide effect size estimates for a future trial and to pilot the data analyses. This will allow us to explore potential data analytic issues that might arise in a large trial such as missingness and skewness. Within-group analyses will be performed for both breast cancer patients and caregivers (see Data Analysis section). For reference, an effect size of *d=* 1.4 for change in depression and anxiety symptoms was found in a prior noncancer sample [18] at 80% power. However, it may not be appropriate to generalize an effect size from a symptomatic depressed sample to an unselected cancer population. For general reference, the smallest effect size that can be detected with a sample size of 25, using paired *t* tests with 80% power and alpha of .05, is *d*=0.58, whereas the smallest effect sizes that can be detected with a sample size of 35, using paired *t* tests with 80% power and alpha of .05, is *d*=0.49 [24].

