### Measures and Outcomes

#### Primary Objective and Measures

Because a significant barrier to conducting this study is the enrollment of participants in a busy clinical setting, we will consider the study feasible if (1) we are able to recruit 1 to 2 participants per week from a single clinic over 29 weeks; (2) complete follow-up in at least 50% of all recruited subjects; and (3) observe a median app launch rate of around 3.0, as found in prior work [18]. Participants will be asked to provide feedback on the apps and coaching at the end of the study period. The Usability, Satisfaction, and Ease of use (USE [28]) short form scale will be used to examine usability of the IntelliCare apps. It is composed of items that assess user experience (eg, “I would recommend it to a friend,” “It is easy to learn to use it,” and “It is simply to use”). Items are scored on a 7-point Likert scale (1=strong disagree and 7=strongly agree). The USE measure is a validated scale that is commonly used to evaluate user experience of digital interventions. Participants will be asked to describe the most positive and negative aspects of the apps and which apps were most and least helpful and why. If participants stopped using the apps, they will be asked to comment on why and barriers to using the apps.

Participants will also be asked to provide open-ended feedback. Research staff will conduct telephone interviews with participants, which will cover the following topics related to using the apps: general impressions, design quality, technical needs, and design suggestions to promote app implementation and usage. In addition, participants will be asked to provide feedback on the following aspects of phone coaching: general experience with coaches, usefulness of coaching, additional or unmet coaching needs, and suggestions to improve the coaching experience. Thematic analysis will be used to analyze qualitative data gathered from interviews. Data yielded from this mixed-methods approach will be used to make improvements to the apps and phone coaching in future work.

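### Paired t tests on the secondary symptom scores drop everyone without a follow-up survey, while up to 50% loss counts as feasible, so the effect sizes passed to the next trial are open to attrition bias

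*Protocol article*

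**What the plan says.** - **Method.** Data Analysis, protocol article: "changes in outcome measures in both cancer patients and caregivers will primarily be analyzed using paired" t tests. The same paragraph adds: "These analyses will be performed separately for patients and caregivers". No other method is named for estimating mean pre-post change.
- **Accepted loss.** Under Primary Objective and Measures, one of three feasibility criteria is to "complete follow-up in at least 50% of all recruited subjects".
- **Sample size.** Participants: "A target sample size of 50 (25 patients and 25 caregivers) was chosen, given the exploratory nature of this study".
- **Use of the estimates.** Participants makes effect sizes for a future trial, and a trial run of the analyses, a secondary objective. It says this will let the investigators explore "potential data analytic issues that might arise in a large trial such as missingness and skewness". Secondary Objectives and Measures adds that the PHQ-4 and the PROMIS anxiety and depression scores will supply estimates of the treatment effects and their variances.
- **Reference power.** Participants gives detectable effects of d=0.58 for 25 and d=0.49 for 35, from paired t tests at 80% power and alpha .05.

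**The concern.** The method and the retention criterion do not fit together well. Every participant gives a baseline score, but a paired t test without imputation ignores that score when the 7-week survey is missing. If the more distressed (or the less distressed) leave, those who remain start from a different level and regress towards the mean differently. Their mean change is then not that of the people recruited.

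The pilot exists partly to pass such estimates on, and missingness is one of the problems it sets out to study. An analysis that leaves out the incomplete cases gives a later trial little to learn from on that subject. The Limitations section warns about small samples and the lack of a comparison group, but not about attrition.

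**Working it through.** **1. The plan's own figures.** For a two-sided paired t test with n pairs, power comes from the noncentral t distribution with n-1 degrees of freedom and noncentrality d x sqrt(n). At 80% power and alpha 0.05 this gives d=0.584 for n=25 and d=0.487 for n=35. The stated 0.58 and 0.49 are therefore reproduced, but they need 25 and 35 *complete pairs*.

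**2. Pairs left at the accepted loss.** 25 x 0.5 = 12.5, so 12 to 13 pairs per group. The same calculation gives a detectable d of 0.89 (12 pairs) or 0.85 (13 pairs). Power for d=0.58 is 45% to 49%.

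**3. Size of the bias.** Work in baseline SDs, with equal pre and post variances and dropout that depends on the baseline score only:

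bias of completer change = (1 - r) x (proportion lost) x D

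Here r is the pre-post correlation and D is the baseline difference between dropouts and completers. The article gives neither r, nor D, nor a dropout mechanism, so these are assumptions: true change -0.30, r=0.6, and a logistic dropout model with the odds ratio shown per baseline SD.

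| Dropout odds ratio per SD | Retention | D | Bias | Share of 0.30 |
|---|---|---|---|---|
| 1.5 | 50% | 0.39 | 0.4 x 0.5 x 0.39 = 0.078 | 26% |
| 2 | 50% | 0.625 | 0.4 x 0.5 x 0.625 = 0.125 | 42% |
| 2.7 (log-odds 1) | 50% | 0.83 | 0.4 x 0.5 x 0.83 = 0.165 | 55% |
| 2.7 | 75% | 0.85 | 0.4 x 0.25 x 0.85 = 0.085 | 28% |

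The 55% row is 0.165 with D unrounded. In that row the completers show -0.30 + 0.165 = -0.135 if the distressed leave, and -0.30 - 0.165 = -0.465 if they stay.

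**4. Against larger effects.** A paired d is converted to baseline SDs by sqrt(2(1 - r)) = sqrt(0.8) = 0.894. This treats the article's effect sizes as standardised by the SD of change. In the strongest case above (bias 0.165):
- d=0.49 is 0.438 SD, so the bias is 38%.
- d=0.58 is 0.519 SD, so the bias is 32%.
- d=1.4 (the prior non-cancer study) is 1.252 SD, so the bias is 13%.

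**5. What a likelihood model does.** With an unstructured covariance and all baselines included, the same settings give about -0.30 in each row when dropout depends on baseline alone. Simulated at 25 per group with 50% retention, root mean squared error is:

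| Dropout | Completers | Likelihood |
|---|---|---|
| Random | 0.261 | 0.253 |
| Odds ratio 1.5 | 0.268 | 0.257 |
| Odds ratio 2 | 0.285 | 0.268 |
| Odds ratio 2.7 | 0.302 | 0.286 |

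The standard error alone is 0.28 for the likelihood estimate against 0.25 for completers at odds ratio 2.7, and 0.250 against 0.257 under random dropout.

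**6. Where the model fails.** Let dropout depend on the unseen *follow-up* score, with odds ratio 2 and 50% retention. Completers then show about -0.42 or -0.17, depending on who leaves. The likelihood model gives about -0.50 or -0.09, which is further from -0.30 both ways.

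**The case against.** The case against has four parts.

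- **Status.** The primary objective is feasibility, judged on recruitment, follow-up and app launches. A reader might take the word for *mainly* in the Data Analysis sentence to mean that this is the primary outcome analysis. It is not; the symptom scores are secondary. This objection stands.
- **Absence.** The article never says that the analysis is limited to completers, and a condensed article may leave its missing-data rules to the full protocol or analysis plan. No fault can be found in the lack of such a rule. Nor does the text show that missingness will go unexplored, since it can be examined alongside the t tests. What remains is the stated choice of method, which by construction needs both scores.
- **Size.** A reader might infer that the bias exceeds half the true change. That needs a small true change, 50% loss and strong selection together, and 50% is the minimum acceptable retention, not the expected one. The documents do not support it as a general statement. However, the article itself doubts that the earlier d=1.4 carries over to an unselected cancer population, so small changes cannot be set aside.
- **Remedy.** The likelihood model does well in step 5 because dropout there follows its own assumption, and even then the gain in root mean squared error is only about 3% to 6%. Step 6 shows that it can do worse. This stands, and is the reason to report both estimates.

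The article also says that small-sample effect sizes will be read with caution and that clinicians will be consulted on effect size and variance. That tempers the harm but does not address selective loss.

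**Conclusion.** The point holds in a limited form. For the secondary symptom outcomes, the stated method discards baseline scores already collected, at a level of loss that the plan accepts. The resulting effect sizes could rest on 12 to 13 pairs per group.

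If dropout depends on baseline distress, the estimates are biased in a direction that cannot be fixed beforehand. Under the assumed inputs the bias runs from about 26% to 55% of a true change of -0.30 SD at 50% retention. It is about 28% at 75% retention under the strongest selection, and 32% to 38% of the article's reference effects of 0.58 and 0.49 at 50% retention under that same selection. All these shares depend on the assumed correlation and dropout model.

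Nothing here affects the feasibility conclusions. Nor does it show that a likelihood model would recover the true change: that holds only if dropout depends on observed data.

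**What to change.** For each group:

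1. Estimate mean change with a 95% CI from a likelihood-based repeated-measures model with time as fixed effect and an unstructured 2x2 covariance, including every participant with a baseline score. A random intercept alone is not a substitute: it forces equal variances before and after, and can be biased under baseline-dependent dropout when they differ.
2. Report the paired t test beside it, labelled as the completer analysis.
3. Tabulate baseline PHQ-4 and PROMIS scores for completers and non-completers.
4. State that the model assumes dropout depends only on observed data, and show both estimates to whoever plans the later trial.

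The cost is a few lines of code in software the article already names (SPSS, SAS, R), with no new data and no added burden on participants. The standard error may be slightly larger under selective dropout. If dropout depends on the unseen follow-up score, the model can be more biased than the completer analysis, so it should not be presented alone.

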## Results

This study will run for 8 months, and recruitment will be completed by the end of 2018. The study was approved by the local university’s institutional review board. Research staff has been hired and trained, and set up has been completed to store all data on secure university servers. Recruitment commenced in March 2018. As of the end of June 2018, 17 breast cancer patients and 7 cancer caregivers have been consented. We will monitor participants’ progress and continue to recruit participants over the next 4 months or until we successfully hit our target enrollment.

## Discussion

### Principal Findings

A cancer diagnosis impacts both patients and their loved ones. Over a third of US cancer patients experience clinically significant mental distress [34]. Studies also show a high level of distress in cancer caregivers in the United States, with over 25% screening positive for depression and 35% screening positive for anxiety [35]. Unfortunately, face-to-face models of mental health care are not sufficient to meet the growing demand for mental health resources in cancer populations. Mental health and support apps may, therefore, address a critical health care gap, although few studies have evaluated the impact of mental health apps in cancer populations. To understand whether existing mental health apps can benefit cancer populations, it is important to understand their preferences for using them as well as gather information about how these apps can be tailored for cancer populations. Findings from this study will help to address this weakness in clinical care, by providing preliminary data to estimate the effect of a suite of mobile phone apps on mental health outcomes in breast cancer patients and caregivers, as well as tailor an existing intervention to better suit the needs of cancer patients and caregivers. In addition, although some studies have found unique benefits of interventions target patient-caregiver dyads [36], this study will be among the first to examine the preliminary effects of providing mental health apps to patient-caregiver dyads.

Although many apps are available on app stores, digital health technologies (which include apps, wearable sensors, and internet-delivered interventions) that are connected to a care manager in a health care setting are increasingly being used as a method of providing technology-enabled services [37,38]. Such systems can be managed by care managers, physician assistants, nurses, or other trained individuals. Although pairing an app with light coaching is a potential limitation to scalability and real-world implementation in some settings, studies such as these are critical to continue to explore the practicality and feasibility of these blended interventions (ie, interventions that combine an automated intervention with some provision of human support) as well as identify which users may or may not need human coaching or additional human support in larger trials.

Findings from systematic reviews indicate that despite a plethora of mental health apps available in app stores, only a few are empirically supported [8,9,39] and the few that target cancer populations have little to no empirical support [6]. IntelliCare apps are publicly available through both the Google Play store (for Android phones) and the App Store (for iPhones) and have been tested in individuals with clinical mood symptoms [18]. These factors create an ideal situation to conduct a pilot study in cancer patients and caregivers. Findings from this study will extend existing work on how mobile technology can be used to address mental health needs in cancer populations.

### Limitations

This study should be interpreted in light of several limitations. Because the focus of this study is to conduct a pilot study of a potential phase III trial, the sample size will be relatively small and there will be no comparison condition. Thus, it is impossible to rule out the possibility that improvement in psychosocial outcomes is because of IntelliCare apps or outside factors. We also recognize that effect sizes obtained from relatively small sample sizes can be somewhat unreliable and, thus, will be interpreted with caution [40,41]. Recruiting a larger sample size, combined with an RCT design, is an appropriate next step to understand whether using the IntelliCare apps leads to improvement compared with standard treatment. Furthermore, because this study will be recruiting individuals directly from the clinic to achieve the targeted sample size, there are few exclusion criteria that may lead to potential confounders (eg, psychiatric diagnosis). In addition, this study is conducted in a US National Cancer Institute designated clinical cancer center, and therefore, findings may have limited generalizability to settings that do not possess as many resources. Thus, we hope that data from this pilot study will inform future work that attempts to administer IntelliCare apps from those recruited from a range of clinical settings.

It should be noted that some individuals may not possess a personal mobile phone or have a data plan that allows them to participate in this study. Our strategy to help mitigate this problem will be to provide interested participants who do not have a mobile phone with an Android device and an unlimited data plan to ensure equal access to the mHealth intervention. Given that mobile phone ownership, comfort using phones, and the role of mobile phones in daily life are all interconnected, it is important to acknowledge that problems with generalizability will emerge and grow as time elapses from the end of the trial. Providing people with a mobile phone, therefore, only addresses part of this complex problem that impacts the broader field of mHealth. Similarly, future research may wish to examine barriers to scalability of mHealth interventions for cancer populations. For example, to supplement individuals with limited or prepaid phone plans, researchers may want to examine the feasibility of a partial payment plan that would enable users to upgrade their plans. What this pilot study will also provide is an estimate of the approximate percentage of individuals who require a mobile phone in future trials. Finally, to address low literacy of using technology and mobile devices, phone coaching will provide participants with any needed instructions on how to download, use, and manage the IntelliCare apps. Coaches will also be available to provide technical support as needed.

### Conclusions

Very little work has examined the potential effectiveness of mental health apps in cancer patients and their informal caregivers. This pilot study will provide preliminary data regarding the usability and acceptability of a suite of mental health apps in a sample of cancer patients and caregivers in the United States. The mixed-methods approach to gathering user feedback will provide a rich dataset that will guide improvements to the apps and coaching procedure in future studies.

## Abbreviations

CaSES: Caregiver Self-Efficacy Scale
CBT: cognitive behavioral therapy
mHealth: mobile health
PHQ-4: Patient Health Questionnaire-4
PROMIS: Patient-Report Outcomes Measurement Information System
RCT: randomized controlled trial
SMS: short message service
